#### SUSAR

Treatment may re-commence upon conclusion of the deliberations on causality of the SUSAR.

#### Acute kidney injury (AKI)

AKI will be defined as a serum creatinine > 120 µmol/l (59) or anuria (<0.1 ml/kg/h) for more than 24 h (60). Such AKI will necessitate temporary stopping of anakinra administration. Administration can be recommenced once renal function improves (serum creatinine < 120 µmol/l and urine output >0.5 ml/kg/h for at least 24 h). The need to withhold anakinra following AKI will be reassessed after analysis of Stage 1 (n=6 infants), including anakinra plasma concentration data, noting that the recommended dose adjustment in children and adults is alternative daily, in all degrees of renal impairment less than 30 ml/min/1.73 m^2^.

#### Drug-induced liver injury

Drug-induced liver injury will be monitored for as described above and responded to as follows:

1. An increase in ALT to greater than 3x upper limit of normal (ULN) requires repeat within 48 h, including INR.2. Anakinra should be held if ALT >5x ULN.3. Anakinra will be permanently ceased if:ALT >8x ULNALT >5x ULN for 2 weeksALT >3x ULN and INR>1.8ALT >3x ULN with eosinophilia (>5%) (61)

Anakinra can be restarted when ALT fall <3x ULN.

#### Serious infection

Anakinra at higher doses (>100 mg SC daily in adults) has been associated with an increased risk of development of infection (25). However, whether or not it is sensible to withhold anakinra in an individual who develops an infective episode is unclear. Anakinra has been used in large randomised controlled trials of sepsis (>1000 patients) as well as syndromes associated with cytokine storm, showing some evidence of benefit and no signal of increased morbidity/mortality (62). In the sepsis trials, anakinra was given over the initial 72 h (57), thus safety in the setting of infection beyond 72 h cannot be assumed. In the event of a positive blood culture and clinical signs of sepsis, anakinra will be withheld if the neutrophil count is <0.5 x 10^9^/l and/or circulatory support with infusion of inotropic medications is required and cannot be weaned 48 h after commencement. Anakinra can be recommenced with recovery of the neutrophil count to >0.75 x 10^9^/l or cessation of inotropic treatment.

### Safety monitoring

All participating infants will be monitored closely following the infusion of anakinra as is standard clinical practice at Monash Children’s Hospital’s Neonatal Intensive Care Unit (NICU) and most other NICUs, with particular attention to vital signs in the 10 min immediately after the administration of anakinra. Adverse event (AE) reporting will be commensurate with the clinical course expected for the study population of extremely preterm infants.

Adverse Events are defined as:

• Any untoward medical occurrence in a patient enrolled into the study• Sustained unexpected change of 30% or more from baseline vital signs (heart rate, blood pressure, respiratory rate, oxygen saturation, body temperature) within 10 min of anakinra administration• Unexpected need to escalate respiratory support within 12 h of anakinra administration• Unexpected need to initiate or escalate inotropic support within 12 h of anakinra administration• Any event requiring cardiopulmonary resuscitation that occurs within 12 h of anakinra administration will be investigated as a potential serious AE.

To assess safety, the following monitoring will be conducted:

1. Early respiratory outcomes will comprise mode of ventilation, lowest pH, highest pCO_2_, highest FiO_2_ and highest mean airway pressure or continuous positive airway pressure (CPAP) level. The respiratory index will be calculated from the last 2 items. Each of these parameters will be recorded daily for the entire treatment duration, and on postnatal day 42. We will also record:

a) each intubation event up to postnatal day 42, including the reason for intubation (e.g. FiO_2_ requirement, respiratory acidosis, apnoea, other);b) surfactant administration (number of doses);c) administration of inhaled nitric oxide (yes/no);d) maximum maintenance caffeine dose used (mg/kg/day).

For analysis purposes, we will further record:

e) Maternal clinical data from the ante- and peri-natal period, including duration of rupture of membranes, maternal fever, chorioamnionitis, antibiotic therapy, maternal medication (including antenatal steroids and magnesium sulfate), hypertension, gestational diabetes, abnormalities of antenatal ultrasounds, and other conditions relevant to the wellbeing of the infant; andf) mode of delivery, Apgar score and resuscitation.

2. Later cardiopulmonary outcomes will comprise duration/last day receiving of:

a) mechanical ventilation;b) respiratory support including CPAP and high flow;c) supplementary oxygen.d) Moreover, we will record total days of mechanical ventilation, high frequency oscillation and postnatal steroids; BPD [yes/no, Jensen grade (63)]; pulmonary hypertension (yes/no by echocardiography at ~36 weeks corrected GA); and discharge to other hospital or home on respiratory support or oxygen.

3. From blood tests obtained for clinical reasons, in addition to the parameters already mentioned above, the following will also be recorded: Full blood counts, urea, electrolytes, creatinine, liver enzyme studies, blood cultures and viral swabs. Monitoring of cellular and plasmatic immunology will be conducted on blood samples and of the microbiome on stool and respiratory samples.

4. From the clinical charts, we will monitor the occurrence of sepsis, necrotising enterocolitis, intracranial haemorrhage and medications.

5. Infants will receive cranial ultrasounds according to standard monitoring protocol on days 3, 8, 14 and 42 after birth. They will also have a magnetic resonance scan (MRI) of the brain at term-equivalent age, i.e. at 38-42 weeks GA, in which brain structure, and presence or absence of dWMI will be assessed in detail. For this purpose, a scoring system will be used wherein white matter will be graded on a scale of 0-4 for the following six variables: 1) cystic degeneration, 2) focal signal abnormalities, 3) delayed myelination, 4) thinning of the corpus callosum, 5) dilated lateral ventricles, and 6) reduction of WM volume as per (64).

6. Although not part of the trial’s primary safety outcomes, early neurodevelopmental assessments will be undertaken in the neonatal period [General Movement Assessment (GMA-writhing period (65)], Hammersmith neonatal neurological examination (HNNE) (66), orthopaedic assessment (plagiocephaly, hip dysplasia) and screening for early diagnosis of cerebral palsy and significant motor delay at 3-4 months corrected age (GMA-fidgety period, Hammersmith infant neurological examination (HINE) (67), orthopaedic and infant feeding screening assessments) in the Monash Newborn Early Neurodevelopment Clinic.

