### Exclusion criteria

• Inability of the legal guardians to consent.• Any disease or condition that the investigators judge could confound the trial results; these include, but are not limited to, genetic syndromes, severe cardiac or other abnormalities, substantial pre-/perinatal compromise (postnatal hypoxia (SaO2<80% for >3h), intrauterine stroke and others.• Imminent death.• Foreseeable inability to adequately excrete anakinra, i.e. severely and permanently compromised renal function.

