### Sample size

We will recruit 24 infants. Given the well-established, favourable safety profile and extensive clinical experience with anakinra, including in children and infants, as well as detailed knowledge on its mechanism of action, this number of participants will suffice to demonstrate safety and feasibility. In addition, it will allow confirmation of predicted/simulated drug disposition, by comparing observed concentration with the population PK simulation, to inform dose selection for future large effectiveness trials.

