### Definitions

#### Safety

For the purposes of the trial’s primary objective, safety will be defined as completion of the described treatment regimen in our target population, without any adverse events of greater frequency or severity than expected to be observed in this high-risk population. For example, at Monash Newborn the baseline rate of late-onset sepsis in this population is 27%, early-onset sepsis is 1%, death is 15%, BPD is 70% and necrotising enterocolitis is 12%.

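### The 30% vital-sign trigger for adverse events cannot operate for body temperature and is insensitive for oxygen saturation, so recording of reactions in those two signs rests on judgement

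*Protocol article*

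**What the plan says.** The Safety monitoring section of the protocol article says that infants will be watched closely after each infusion, "with particular attention to vital signs in the 10 min immediately after the administration of anakinra". It then lists what counts as an adverse event:

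- The first item is general and has no threshold: "Any untoward medical occurrence in a patient enrolled into the study".
- The second is the vital-sign item: "Sustained unexpected change of 30% or more from baseline vital signs (heart rate, blood pressure, respiratory rate, oxygen saturation, body temperature) within 10 min" of a dose.
- Further items cover increased support in the 12 hours after a dose, for example "Unexpected need to escalate respiratory support within 12 h of anakinra administration", with parallel items for inotropes and resuscitation.

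The section also states that "Adverse event (AE) reporting will be commensurate with the clinical course expected for the study population of extremely preterm infants".

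These events matter for the primary aim. The Safety definition requires completion of the regimen "without any adverse events of greater frequency or severity than expected to be observed in this high-risk population". The Data Safety Monitoring Board section has the board review adverse incidents after the first 3 and the first 6 infants, and agree Stage 2 dosing with the investigators after the sixth.

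**The concern.** A relative limit suits a sign whose plausible range is wide compared with its usual value. Heart rate, respiratory rate and blood pressure are of that kind. Temperature in degrees Celsius and oxygen saturation are not: clinically relevant changes are small fractions of the baseline value, and saturation also has a ceiling of 100%. The same 30% therefore means something quite different for each of the five signs listed.

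This is the only adverse-event item with a numeric limit on a physiological sign, and it covers the minutes after dosing that the protocol itself singles out. If it cannot work for two of the five signs, whether a temperature or saturation reaction is recorded depends on whoever is at the cot side. The trial is single-arm, and its primary safety definition turns on the frequency and severity of adverse events, so uneven recording has no concurrent comparator to offset it.

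**Working it through.** The 30% is a chosen threshold, not the result of a formula, so there is no figure of the plan's own to reproduce. The check is what the threshold implies for each sign.

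**Inputs**
- From the protocol article, Safety monitoring: a change of at least 30% from baseline, either direction, within 10 minutes of a dose.
- From the protocol article, Exclusion criteria: "postnatal hypoxia (SaO2<80% for >3h", given as an example of substantial compromise. It is used here only as a benchmark for level, not duration.
- Assumed, because the documents give no baseline vital signs: temperature 36.0 to 38.0 °C; saturation 85 to 100%; and, for comparison, heart rate 150/min, respiratory rate 50/min and mean blood pressure 30 mmHg.

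**Formula**

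Lower limit = baseline × 0.70; upper limit = baseline × 1.30.

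**Temperature**

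| Baseline (°C) | Lower limit | Upper limit | Shift needed |
|---|---|---|---|
| 36.0 | 25.2 | 46.8 | 10.8 |
| 37.0 | 25.9 | 48.1 | 11.1 |
| 38.0 | 26.6 | 49.4 | 11.4 |

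For scale, a 2 °C change is 2/38 = 5.3% to 2/36 = 5.6% of baseline, far short of 30%.

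**Oxygen saturation**

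| Baseline (%) | Lower limit (%) | Relative size of a fall to 80% |
|---|---|---|
| 85 | 59.5 | 5/85 = 5.9% |
| 92 | 64.4 | 12/92 = 13.0% |
| 100 | 70.0 | 20/100 = 20.0% |

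A rise of 30% is impossible from any baseline above 100/1.30 = 76.9%. Even from 100%, a fall to the 80% benchmark is a 20% change, so it does not meet the item from any baseline in the range.

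**The other three signs**
- Heart rate 150/min: limits 105 and 195.
- Respiratory rate 50/min: limits 35 and 65.
- Mean blood pressure 30 mmHg: limits 21 and 39.

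These limits are attainable, so the difficulty is confined to temperature and saturation.

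**Alternative reading**

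If 30% was meant as an absolute change, the text does not say so, and it would not help: 30 percentage points of saturation from 92% is a fall to 62%.

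**The case against.** The strongest reply is that the vital-sign item does not stand alone. A reader might infer from the arithmetic that infusion reactions in temperature or saturation would go uncounted. The document does not support that. The first item on the same list makes any untoward occurrence an adverse event without a threshold, nothing says that a change below 30% is not an adverse event, and a desaturation that leads to more support falls under the respiratory item. The support and resuscitation items are also observable, charted events, so the vital-sign item is not the only objective criterion. Daily respiratory data and continuous physiological data are collected too, although 24-hour summaries are no substitute for an acute trigger. All of this stands, and it limits the point to ascertainment rather than capture.

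It does not remove the point. A specific item is there to standardise what a general item leaves open. Staff given a 30% limit may take smaller changes to be below threshold, and the statement that reporting will match the expected clinical course leaves further discretion.

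A second tempting inference concerns the 12-hour windows. Alternate-day dosing over 21 days gives 11 × 12 = 132 of 504 hours (26%); daily dosing gives 21 × 12 = 252 hours (50%). A reader might conclude that the higher dose will look worse by construction. The arithmetic is right, but the article states no between-stage comparison of these counts. The items are restricted to unexpected need, the general item has no window, and the specified board reviews, after 3 and 6 infants, involve Stage 1 infants only. No bias follows from the text.

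**Conclusion.** The point holds in a limited form. For two of the five signs that the protocol chose to list, the numeric trigger does not do its job: for temperature it is inoperative, needing a shift of about 11 °C within 10 minutes, and for saturation it is insensitive, needing a sustained fall to about 60 to 70%. A fall to the protocol's own 80% benchmark is a change of 5.9 to 20.0% and never qualifies. These figures rest on the assumed baselines of 36 to 38 °C and 85 to 100%; no value within those ranges changes the conclusion.

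The consequence is inconsistent recording, not loss of the events. Reactions in these signs remain reportable, but by judgement, and those judgements feed the primary safety definition and the board's review before Stage 2. The size of any under-recording cannot be estimated from the document. The arithmetic is certain and the practical effect is minor to moderate. The correction is cheap and should be made.

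**What to change.** In the adverse-event list under Safety monitoring, keep the 30% relative criterion for heart rate, blood pressure and respiratory rate. For body temperature and oxygen saturation, replace it with criteria specific to each sign and expressed as an absolute change, with values set by the sponsor's clinical team; the documents give no basis for proposing values here. Keep the general item, so that a change short of any limit can still be reported.

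The cost is a change to the adverse-event wording. The downside is some more adverse events to record.

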### Blood sampling procedure

Central or peripheral catheters will be used whenever possible. If no catheter is available, blood will be obtained by heelprick or venipuncture performed for routine diagnostic blood sampling whenever possible. Thus, exposure of the patients to painful procedures outside routine clinical care is minimised. We obtain 0.5-1 ml of blood (0.5 ml if patient weight is currently <1 kg, 0.8 ml if 1-2 kg, 1 ml if >2 kg) for each sampling timepoint to perform PK and cellular and plasmatic immune analysis on each sample.

PK blood samples will be taken:

1. From cord blood (baseline)2. On days 1, 3, 7 and 14 of postnatal life. These samples will be collected within 21-23 h post anakinra administration3. 21-23 h after the last dose of anakinra, i.e. on day 22.

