#### b) Maturation

After birth, renal function typically is sluggish in extremely premature neonates, with median inulin clearance expected to be <2.5 ml/min for the first 3 weeks after birth (duration of dosing) (48). Scaled for size, this is below the threshold of 30 ml/min/1.73 m^2^ (49–51), with overall clearance of anakinra thus expected to be reduced by 75% and alternate daily dosing being recommended. For prediction of renal function, a maturation model was used (52), which estimates GFR as a fraction of adult size-scaled equivalent based on post-menstrual age and size. The model was developed from a pooled population analysis of GFR (n=923) using ideal markers of GFR (polyfructose, 51Cr-EDTA, mannitol or iohexol) (52).

Non-renal clearance mechanisms of anakinra have not been described, and caution is required in new drug use in premature neonates due in part to immaturity of various hepatic drug-metabolising enzymes (53). However, no such immaturities have been described for proteolysis of therapeutic proteins (54), and indeed increased endogenous proteolysis has been described in some instances (55). Further, noting the near-identical structure to endogenous IL-1Ra, it would presumably share the same proteolytic pathways, for which there is no evidence of immaturity in the newborn period [plasma abundance of endogenous IL-1Ra in term infants was 42 ± 69 pg/ml on day 1, falling to 27 ± 77 pg/ml on day 2-3 (56)]. Nevertheless, given limited data on therapeutic proteins in extremely premature infants and thus on a precautionary basis, simulations were performed both with assumption of mature and immature non-renal clearance to better understand the impact on exposure if indeed the specific proteolytic mechanism were to be immature.

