However, if this predicted optimal dosing rate of 1.5 mg/kg daily were used from the start and non-renal clearance were immature, this dosing rate would lead to excessive exposure, beyond that seen in older children receiving 3 mg/kg daily of anakinra. This eventuality is avoided with the planned staged approach, in which the first 6 participants receive 1 mg/kg alternate daily, followed by interim PK analysis. The rationale for this decision is as follows. Keeping the threshold of 9.6 mg/l x h in mind beyond which sufficient anti-inflammatory activity can be expected (28), **Figure 3** depicts simulations in studied populations (A-E) and extrapolated populations (F-I), with F and G depicting the predicted exposure if non-renal clearance is fully mature, H and I if non-renal clearance is only 25% mature. Assuming mature non-renal clearance, the stage 1 dosing regimen of 1 mg/kg alternate daily predicts exposure equivalent to 1 mg/kg in a child weighing 12 kg, whilst Stage 2 (optimal) dosing of 1.5 mg/kg daily predicts exposure equivalent to 3 mg/kg in a child of 12 kg. Interim analysis after the first six participants will allow confirmation of non-renal clearance being mature, and enable safe progression to the 1.5 mg/kg daily dosing schedule. On the other hand, in the unlikely case that non-renal clearance is immature (for example at 25% maturity), the initial dosing regimen of 1 mg/kg alternate daily will lead to exposure close to that seen with dosing rate of 3 mg/kg daily in an older child. If non-renal clearance were found to be immature at interim analysis, dosing in Stage 2 would be adjusted accordingly.

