### Summary dosing strategy

For Stage 1, six infants will receive 1.0 mg/kg IV given alternate daily from day 1 to day 21 after birth. In the event of acute kidney injury (AKI), detection during blood monitoring within the 3 weeks of treatment, anakinra treatment will be halted until renal function has recovered as defined below.

After completion of Stage 1, the Investigators and the data safety monitoring board (DSMB) will conduct an interim analysis, including assessment of mortality and rate of complications of prematurity, and comparison of observed exposure with the predicted exposure estimated from the population PK simulation. If appropriate, with confirmation of mature non-renal clearance within the first cohort of 6 infants, Stage 2 will administer 1.5 mg/kg per day for the remaining 18 infants. Furthermore, dosing will not need to be withheld in the setting of acute kidney injury (AKI) if non-renal clearance is confirmed to be mature from birth.

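### With every post-dose PK sample at 21-23 h, the interim can check AUC or confirm mature non-renal clearance only by borrowing the volume of distribution from adults and older children

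*Protocol article*

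**What the plan says.** Under Blood sampling procedure, the PK samples are cord blood, days 1, 3, 7 and 14, and one after treatment ends. For the four numbered days, "These samples will be collected within 21-23 h post anakinra administration"; the final one comes "21-23 h after the last dose of anakinra, i.e. on day 22". No early or mid-interval sample is listed.

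Under Summary dosing strategy, the interim after six infants includes "comparison of observed exposure with the predicted exposure estimated from the population PK simulation", and the condition for escalation is explicit: "with confirmation of mature non-renal clearance within the first cohort of 6 infants, Stage 2 will administer 1.5 mg/kg per day". The same confirmation also decides whether dosing is withheld in acute kidney injury. Section d) Simulations states that "Interim analysis after the first six participants will allow confirmation of non-renal clearance being mature".

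Predicted exposure is an AUC0-24 (Figure 3 caption), set against a threshold of 9.6 mg/l x h. The first secondary objective and the Dose selection section describe the check as measured concentrations set against the simulation.

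**The concern.** After an IV dose, the level at one fixed time is a single equation in two unknowns, clearance (CL) and volume (V). Exposure is dose/CL, so it cannot be read from that level unless V is supplied from elsewhere. Every volume in Table 2 comes from adults or older children, and the Dose selection section reports no use in extremely premature neonates.

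The interim decides whether the dose rate goes from 1 mg/kg per 48 h (0.5 mg/kg/day) to 1.5 mg/kg/day, a threefold rise, and whether the kidney-injury hold is dropped. If the borrowed V is wrong, partly immature clearance can be read as mature, or the reverse. The error would be common to all six infants, so averaging over them would not reduce it. Pharmacokinetics is also one of the three aims in the trial's title.

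**Working it through.** **Inputs from the article.** Reference infant 850 g; Stage 1 dose 1 mg/kg, so 0.85 mg. CL 6.24 l/h/70 kg and V 6.52 l/70 kg (paediatric analysis, Table 2); published V from 5.14 to 9.99 l/70 kg. Exponents ¾ for CL and 1 for V. Renal share of clearance about 75%, with total clearance expected to fall by 75%. Endogenous IL-1Ra: "plasma abundance of endogenous IL-1Ra in term infants was 42 ± 69 pg/ml on day 1".

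**Assumptions.** One compartment, bolus dose, 20% residual error. CL = 6.24 x (WT/70)^0.75 x (0.75f + 0.25m), where f is renal maturation and m is non-renal maturity. The article's 75% reduction is f = 0, m = 1; f = 0.1 is a sensitivity value. Stage 1 AUC0-24 is half the AUC per dose.

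**1. Reproducing the plan's exposure equivalence.**
- 12 kg child: CL = 6.24 x (12/70)^0.75 = 1.662 l/h. AUC is 12/1.662 = 7.2 for 1 mg/kg and 36/1.662 = 21.7 for 3 mg/kg.
- 850 g infant, mature non-renal clearance: CL = 6.24 x 0.03658 x 0.25 = 0.05706 l/h. AUC0-24 is (0.85/0.05706)/2 = 7.4 in Stage 1 and 1.275/0.05706 = 22.3 in Stage 2.

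These agree within about 3%, so the simple model matches the article's stated equivalence.

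**2. What samples at 21-23 h identify.** ln C(t) = ln(D/V) - (CL/V)t. If all t are 22 h, the information matrix for (ln CL, ln V) has rank 1. Five samples spread evenly over 21-23 h, with V unknown, give SE(ln CL) of about 2.6 per infant, which is practically no information. Repeat visits add no second equation: the Stage 1 accumulation ratio 1/(1 - exp(-48 CL/V)) is 1.00 in every scenario, and the article itself reports no Stage 1 accumulation.

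**3. Level at 22 h (pg/ml), f = 0.** Worked example at V 9.99, m = 1: V = 9.99 x 0.85/70 = 0.1213 l; k = 0.05706/0.1213 = 0.470/h; C = (0.85/0.1213) x exp(-0.470 x 22) = 2.24 x 10^-4 mg/l = 224 pg/ml.

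| V (l/70 kg) | Mature (AUC0-24 7.4) | 50% (14.9) | 25% (29.8) |
|---|---|---|---|
| 5.14 | 0.025 | 584 | 89,200 |
| 6.52 | 1.4 | 3,870 | 204,000 |
| 9.99 | 224 | 39,700 | 527,000 |

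- Down the mature column AUC is constant, yet the level changes about 9,000-fold (224/0.025) with the choice of published V.
- Mature clearance at V 9.99 and half-mature clearance at V 5.14 differ 2.6-fold in level (584/224) and twofold in AUC.
- With mature clearance the half-life, ln 2/k, is 0.76-1.47 h, so 22 h is about 15-29 half-lives. The expected 0.025-224 pg/ml lies below or overlaps the quoted endogenous range (42 + 2 x 69 = 180 pg/ml); only the largest volume goes slightly above it.

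**4. One level, many exposures.** Holding the 22 h level at its value for V 6.52 and solving for CL across V 5.14-9.99:

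| Truth | Stage 1 AUC0-24 that fits | Implied m |
|---|---|---|
| m = 1, f = 0 | 5.0-9.3 | 0.80-1.49 |
| m = 0.5, f = 0 | 10.3-18.3 | 0.41-0.72 |
| m = 0.5, f = 0.1 | 6.3-11.6 | 0.34-0.88 |

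The last row straddles 9.6. In general d ln CL/d ln V = 1 - 1/(kt) at fixed C. With kt = 0.721 x 22 = 15.9 this is 0.94, so an error in V passes almost one for one into CL.

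**5. What earlier samples would add.** Take samples at 1 h and 6 h, V 6.52, mature, and write y for ln C. Then ln V depends on 1.2 y1 - 0.2 y6, so SE(ln V) = 0.2 x sqrt(1.44 + 0.04) = 0.24. For ln CL the weights on y1 and y6 are -0.92 and -0.08, so SE(ln CL) = 0.2 x sqrt(0.92² + 0.08²) = 0.18. The level at 6 h is (0.85/0.0792) x exp(-0.721 x 6) = 0.142 mg/l = 142,000 pg/ml, far above the endogenous level.

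**The case against.** The planned check is not a stand-alone fit. The secondary objective and the Dose selection section set measured concentrations against a simulation that already carries V, its scaling and between-patient variability. If V is taken as known to 25% (an assumption), SE(ln CL) from five samples at 21-23 h falls from about 2.6 to about 0.23 per infant. A reader might therefore infer too much from the rank argument, namely that AUC cannot be estimated at all or that the interim is blind. The documents do not support that. AUC can be estimated conditionally on a borrowed V.

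The staging is chiefly motivated by the case of 25% maturity, and that case would show. At f = 0 it gives at least 89,200 pg/ml against at most 224 for mature clearance; at f = 0.1, at least 214 against at most 10. With CL 6.96 and f = 0 the ranges are about 50,000-391,000 against at most 68. Nor can a large volume alone imitate gross immaturity at the same f within Table 2's range. At a common V of 6.52, half and full maturity are also far apart (3,870 against 1.4 pg/ml), so confusing them requires the true and assumed V to lie towards opposite ends of the range.

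Table 2 also reports initial volumes of about 3 l against 9-10 l, which points to more than one compartment. A slower late phase would change the pg/ml figures, possibly greatly, and the endogenous figures are from term infants. The interim also weighs mortality and complications, with board review after 3 and 6 infants, and blood volume is a real constraint.

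What stands against all this is that the conclusion on maturity depends on a V never measured in this population. A further compartment adds unknowns and does not remove the confounding. A separate PK analysis plan could not recover information that the listed times do not contain.

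**Conclusion.** The point holds in a limited form. The trial's own samples cannot separate clearance from volume, so observed AUC0-24, and the distinction between full and about 50% non-renal maturity, rest on a borrowed V. Over the published range this leaves about a 1.9-fold span in AUC (5.0-9.3 when clearance is mature). It also allows full and half maturity to give similar 22 h levels at the extremes of V. If clearance is mature, as the plan expects, the 22 h level is mostly at or below the endogenous background and says little beyond the absence of gross immaturity. The interim can rule out 25% maturity, but it cannot reliably deliver "with confirmation of mature non-renal clearance within the first cohort of 6 infants" or an observed AUC0-24 to set against the prediction.

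This rests on a one-compartment bolus model, f of 0-0.1 and Table 2's volumes. It is a cheap improvement worth making before the Stage 1 data are collected, not a reason to regard the PK work as void.

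**What to change.** Keep the present number and volume of samples. Move some of the existing postnatal samples to early and mid-interval windows, for example about 0.5-2 h and 4-8 h after a dose, and keep some at 21-23 h, where they still detect gross immaturity. Choose the windows by running candidate schedules through the existing simulation model, and record exact dose and draw times. Estimate CL and V jointly, and give the interim review the estimated AUC0-24 with its interval.

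Do not add a sample just before the next Stage 1 dose. At 46 h with mature clearance and V 9.99 the model gives 7.01 x exp(-0.470 x 46) mg/l, about 0.003 pg/ml, which is far below the endogenous level.

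The cost is wording in the protocol and laboratory manual, coordination of draws with line access and routine sampling, and varying time since dose for the immune assays run on the same blood, which can be handled as a covariate. The change concerns sampling times and reporting only; it implies nothing about dose or about when treatment should be withheld.
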